#### Secondary aims

To assess sustainability, HPV vaccination rates will be calculated at month 36 (12 months post-intervention). The change in HPV vaccination rates between month 24 and month 36 (12 months post-intervention) will be tested by McNemar test. The intervention will be deemed as sustaining its effect if rates of HPV vaccine initiation rates at month 36 remains or increases from month 24’s vaccination rates. To inform future scalability of the program, data from the evaluation and post-evaluation surveys will be described using summary statistics (e.g., quartiles, median, mean, standard deviation) for continuous variables and marginal distribution (frequency and percentage) for categorical variables. The similar analyses will be repeated within each of the three clinics. Additionally, we will conduct a post-intervention focus group consisting of the providers and clinic staff that participated in the program. The qualitative evaluation explore how implementation took place; the barriers to and facilitators of implementation success; ways to address any problems that may have occurred; and recommendations to refine the intervention for scale-up. The focus session will be recorded and transcribed where themes will be extracted and used for adaptation, scale-up considerations, and future research directions.

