## Methods/design

A pre-post intervention study design is used where HPV vaccination initiation and completion rates are measured before and after the intervention across the same clinics and enrolled participants (Fig. 1). HPV vaccination uptake 18 months before intervention will be queried from electronic medical records (EMR) and Georgia Registry of Immunization Transactions and Services (GRITS), which will serve as the historical control. GRITS is a population-based web application containing consolidated demographic and immunization history information. The use of a concurrent control is to reassess the background HPV uptake rate among PLWH during an adjacent time-period to post-intervention and similar population resources. The comparison of HPV vaccination rates pre- and post-intervention in the three selected representative HIV clinics in Georgia will be an exploratory goal of the trial due to the retrospective approach in the control phase and the prospective approach in the post intervention phase. A “within” analysis will be conducted to compare sites both pre- and post-intervention.

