### Data analysis plan

#### Study outcomes

Initiation of the HPV vaccine is the primary outcome endpoint (Fig. 2). Initiation of the HPV vaccine is defined as receiving the first or second immunization from the series. This variable will be measured by electronic medical records and GRITS at baseline (historical control) and 24 months post baseline. We hypothesize the initiation rate will be higher than the historical control rate. Completion of the HPV vaccine is the secondary outcome variable. Completion is defined as receiving all three immunizations from the series, regardless of time. This variable will be measured by electronic medical records and GRITS baseline (control) and 24 months post baseline.

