#### Process evaluation

The RE-AIM (Reach, Effectiveness/Efficacy, Adoption, Implementation, Maintenance) framework will guide planning, implementation, and evaluation of the 4 Pillars™ program. The study’s reach will be estimated from a quantitative perspective by estimating the target population that was exposed to the intervention. The clinic’s patient census data during the period of the implementation phase will be used to estimate the likely reach of the program across sites. Intervention effectiveness and efficacy will be measured by the change in uptake rate of vaccination (i.e., intervention effectiveness). We will calculate the percent change in initiation of the vaccine and percent change in completion of the vaccine from the control phase and 24 months post intervention, after adjusting for demographics differences (age, gender, race, healthcare insurance) in population. Providers and clinic staff will be asked to complete an evaluation of HPV vaccination progress every 3-months. We will also collect qualitative data from feedback sessions with the immunization champions to assess opportunities for and barriers to adoption. The post-evaluation interviews with providers and staff who implemented the program will assess extent of involvement, acceptance of the intervention, implementation fidelity, and extent of organizational spread of the intervention. We will assess the frequency, duration, and the extent to which the intervention was implemented as planned, participation attendance, and costs of implementation, as measured via the intervention and post-intervention evaluations. Intervention sustainability will be measured as the gains or maintenance of HPV vaccination rates post-delivery of the intervention. HPV vaccination rates will be calculated via EMR and GRITS at month 36 (12 months post intervention) and compare to HPV vaccination rates at month 24. Follow up assessments will measure penetration or the extent to which recommendation and administration of the HPV vaccination is integrated within the clinic.

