#### Statistical power

Based on our preliminary data, we found that HPV vaccination rate is around 13.5% (P0) in general, and another larger study in the literature found a very similar rate of 13.6% [10]. We powered the study to detect an uptake rate > 13.5% after the intervention. Thus, a sample size of 317 achieves 80% power to detect a superiority difference of 5% (PB-P0) using an exact one-sided test with a significance level (alpha) of 0.05. We anticipate a 5% superiority difference is reasonable to achieve with an uptake rate of 18.5% (PB) after the intervention. We will be able to reject the Null hypothesis and claim the uptake rate of > 13.5% after 54 patients have initiated the HPV test. After taking about 15% of the drop-off rate into account, we plan to include 365 participants among 3 clinics for the intervention phase. The calculation was by PASS 2020 for testing superiority of one proportion using the Exact test. The Null hypothesis is *P* < = 13.5% and the alternative hypothesis is *P* > 13.5%. For the control phase, we will query all eligible subjects from EMR database among the 3 clinics at 18 months pre-intervention, which could be approximately 2300 subjects [30]. Assuming we end up with the same number of subjects in both control (*N* = 317) and intervention phase (*N* = 317), we will have 81% statistical power to detect an HPV uptake rate difference of 9% (22.5% vs. 13.5%) by two-sided Fishers’ Exact Test and under significance level of 0.05. We anticipate such a difference would be feasible based on our best knowledge and the literature. Regarding the patient- level component of the intervention, all incoming eligible patients will be influenced, and hence 365 participants are the minimum number to capture the follow-up information, the actual number of sample size used for the calculation of HPV vaccination rate will be larger as the vaccination status will be captured automatically in EMR without a consent.

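### The month-36 sustainability rule is uninformative under the paired test it names: among the same patients, initiation can only stay level or rise

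*Protocol article*

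**What the plan says.** Two places in the Protocol article govern sustainability, which is part of Aim 4.

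- **Secondary aims** names the test: "The change in HPV vaccination rates between month 24 and month 36 (12 months post-intervention) will be tested by McNemar test". It then sets the decision rule: the intervention is "deemed as sustaining its effect if rates of HPV vaccine initiation rates at month 36 remains or increases from month" 24. No margin, minimum gain or external comparator is attached.
- **Process evaluation** gives the same measure as the maintenance element of RE-AIM: "Intervention sustainability will be measured as the gains or maintenance of HPV vaccination rates post-delivery of the intervention". The data source is also named: "HPV vaccination rates will be calculated via EMR and GRITS at month 36 (12 months post intervention) and compare to HPV vaccination rates at month" (the earlier time point being month 24).

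The outcomes come from Study outcomes. For initiation: "Initiation of the HPV vaccine is defined as receiving the first or second immunization from the series". For completion: "Completion is defined as receiving all three immunizations from the series, regardless of time". Doses are read from the electronic medical record (EMR) and the state registry GRITS. Methods/design describes the registry thus: "GRITS is a population-based web application containing consolidated demographic and immunization history information". A past dose therefore stays on record.

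Nothing in the article limits the month-36 rate to doses given after month 24, or to patients unvaccinated at month 24.

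**The concern.** A sustainability criterion should be able to say that the effect faded once the programme ended. This one pairs a test that requires the same individuals at both times with an outcome that, once reached, cannot be lost. In that setting the later rate is bound to be at least as high as the earlier one, so the conclusion is known before the data exist.

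It is the only quantitative sustainability criterion in the article, and Aim 4 also looks ahead to a national randomised trial. A finding that the effect was sustained would carry weight there. Under the named test, that finding would be the same whether vaccination continued at full pace or stopped entirely at month 24.

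**Working it through.** The article gives no sample size, power or margin for this rule, so there is no stated figure to reproduce. The check is of the paired table.

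**Inputs.** From Statistical power: 317 evaluable and 365 enrolled participants, and the anticipated post-intervention uptake ("We anticipate a 5% superiority difference is reasonable to achieve with an uptake rate of 18.5% (PB) after the intervention"), used here as an illustrative month-24 rate. The number of new initiations in months 24 to 36 is not given and is varied as an assumption.

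**Step 1: direction of change.** Let b be the patients not initiated at month 24 but initiated at month 36, and c the reverse.

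- Change in rate = (b − c)/n.
- A dose received cannot be un-received, so c = 0 and the change is b/n ≥ 0. The rule is met for every possible b, including b = 0.

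**Step 2: numbers.** 317 × 0.185 = 58.6, taken as 59 initiated (59/317 = 18.6%), leaving 317 − 59 = 258 uninitiated. With c = 0, the exact two-sided McNemar p-value is min(1, 2 × 0.5^b).

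| Share of the 258 newly initiating (assumed) | b | Month-36 rate | p | Rule says |
|---|---|---|---|---|
| 0% | 0 | 59/317 = 18.6% | 1 | sustained |
| 1% | 3 | 62/317 = 19.6% | 0.25 | sustained |
| 2% | 5 | 64/317 = 20.2% | 0.0625 | sustained |
| 5% | 13 | 72/317 = 22.7% | 0.0002 | sustained |

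In 20,000 simulated trials at each of the assumed rates 0%, 1% and 5%, the rule was met every time.

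**Step 3: what the test adds.** It can detect only an increase. At b = 6, p = 2 × 0.5^6 = 0.031. Six is 6/258 = 2.3% of the uninitiated among 317. Among all 365 enrolled, 365 × 0.815 ≈ 297 are uninitiated, and 6/297 = 2.0%. A significant result therefore needs only about 2% of the remaining patients to start in a year, and it is not set against any background pace.

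**Step 4: background pace (assumption only).** Statistical power gives 13.5% without an accrual window. If it accrued over 18, 24 or 36 months, the 12-month equivalent is:

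- 18 months: 1 − 0.865^(12/18) = 9.2%
- 24 months: 1 − 0.865^(12/24) = 7.0%
- 36 months: 1 − 0.865^(12/36) = 4.7%

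Each exceeds 2.0% to 2.3%. If 13.5% is simply the share ever vaccinated, with no defined window, no yearly pace follows from it. Steps 1 to 3 do not depend on this step.

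**Step 5: the open-population reading.** Data analyses of primary outcomes uses all eligible cases, and Statistical power says that rates will rest on more than the 365 because the EMR captures status automatically. If 20% of patients were replaced by newcomers of whom 5% had initiated (both assumed), the rate would go from 18.5% to 0.8 × 18.5% + 0.2 × 5% = 15.8%. The rule can then fail, but through turnover. The two groups are no longer the same people, so McNemar does not apply.

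**The case against.** The strongest reply is that the article does not commit to a closed cohort. A reader might infer from the paired argument that the rule can never fail on any reading. The documents do not support that: on a changing clinic population the rate can drop, as Step 5 shows. This part of the reply stands and limits the claim. It does not rescue the plan, because the named test is then the wrong one and a fall could reflect newcomers rather than a fading effect.

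A second reply is that initiation might mean one or two doses only, with completers leaving the category. Yes-to-no pairs could then occur. If 30% of the 59 initiators completed and 1% of the 258 others started (both assumed), the rate would fall to (59 × 0.7 + 258 × 0.01)/317 = 13.8%. The article does not state this exclusive reading, and under it the rule would penalise completion of the series. Lost records could also produce apparent reversals, but those would be data errors.

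Third, a reader might infer that the test would certainly declare success at a pace below no-programme uptake. That needs a time window for the 13.5%, which the article describes only as a general rate. The 18 months is the look-back for the historical control. The comparison stands only as the assumed range in Step 4.

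Finally, penetration assessments, surveys and focus groups also inform sustainability and scale-up. They do, but they are descriptive and do not alter the stated rule.

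**Conclusion.** The concern holds in a conditional form. Under the paired McNemar test that the article names, with initiation read as having received a dose, the rule is met with certainty, even with no vaccination after month 24. The significance test adds little, since six new initiations are enough for p = 0.031. Under the open-population reading the rule can fail, but the test does not fit the data. Neither reading gives a sound measure of sustainability.

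The paired result rests on two things only: the same patients at both times, and a status that cannot reverse. The 18.5% and the 317 or 365 are illustrative; the background pace is an assumption and not part of the conclusion. Because the rule and the test are both stated, this is not detail left to an analysis plan. The primary and secondary endpoints and the sample size are unaffected. It should be fixed before the month-36 analysis, but it is not critical to the trial's main result.

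**What to change.** Replace the rule and the McNemar test in Secondary aims, and align Process evaluation with the change:

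- **Measure.** The rate of new first-dose initiation in months 24 to 36, per person-month, among eligible clinic patients with no dose at the start of that window, or on entry to it if later.
- **Comparison.** The same measure in the intervention period (months 0 to 24) and in the 18-month historical window, as rate ratios with 95% confidence intervals.
- **Criterion.** Set in advance by the sponsor, and able to fail. One option is that the month 24 to 36 rate remains above the historical rate, for example with the lower confidence limit of the ratio above 1. A margin against the intervention period is another. The choice is the sponsor's.
- **Presentation.** Show newly eligible or incoming patients separately from those already in the clinic at month 24.

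**Cost.** Dose dates should come from the EMR and GRITS query already planned for month 36. Eligibility and attendance denominators are also needed for each window, which is extra extraction work. Patients still unvaccinated after 24 months of promotion may be more hesitant, which biases the comparison towards a finding of not sustained; the separate display of incoming patients addresses this. Sustainability can then fail, which is the purpose of the change.

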#### Statistical power

Based on our preliminary data, we found that HPV vaccination rate is around 13.5% (P0) in general, and another larger study in the literature found a very similar rate of 13.6% [10]. We powered the study to detect an uptake rate > 13.5% after the intervention. Thus, a sample size of 317 achieves 80% power to detect a superiority difference of 5% (PB-P0) using an exact one-sided test with a significance level (alpha) of 0.05. We anticipate a 5% superiority difference is reasonable to achieve with an uptake rate of 18.5% (PB) after the intervention. We will be able to reject the Null hypothesis and claim the uptake rate of > 13.5% after 54 patients have initiated the HPV test. After taking about 15% of the drop-off rate into account, we plan to include 365 participants among 3 clinics for the intervention phase. The calculation was by PASS 2020 for testing superiority of one proportion using the Exact test. The Null hypothesis is *P* < = 13.5% and the alternative hypothesis is *P* > 13.5%. For the control phase, we will query all eligible subjects from EMR database among the 3 clinics at 18 months pre-intervention, which could be approximately 2300 subjects [30]. Assuming we end up with the same number of subjects in both control (*N* = 317) and intervention phase (*N* = 317), we will have 81% statistical power to detect an HPV uptake rate difference of 9% (22.5% vs. 13.5%) by two-sided Fishers’ Exact Test and under significance level of 0.05. We anticipate such a difference would be feasible based on our best knowledge and the literature. Regarding the patient- level component of the intervention, all incoming eligible patients will be influenced, and hence 365 participants are the minimum number to capture the follow-up information, the actual number of sample size used for the calculation of HPV vaccination rate will be larger as the vaccination status will be captured automatically in EMR without a consent.

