The Advancing HPV vaccination for HIV Positive Adults (CHAMPS) study seeks to expand the success of the 4 Pillars™ Program and tailor, refine, and implement in the HIV positive population, who are at high risk for HPV-related cancers and can obtain the most benefit from the vaccine. The strategies selected from the 4 Pillars™ Program are based on an extensive review of the HIV and related literature (Table 2) [21–28]. The intervention will be implemented in three HIV community clinics in Georgia, USA and enroll *n* = 365 PLWH, age 18–45 years, from those clinics. Guided by the RE-AIM framework, the proposed specific aims are:Tailor and refine the 4 Pillars™ program for implementation in three HIV community clinics in Georgia.Test the effectiveness of the 4 Pillars™ program as measured by an increase in uptake rate in initiation of the HPV vaccine (primary outcome) and vaccine completion (secondary outcome) compared to historical baseline vaccination rate (control) among PLWH. It is hypothesized after implementation of the 4 Pillars™ program, we estimate an uptake rate of > = 13.5% in initiation of HPV vaccination.Identify mediators and potential moderators (HPV knowledge and awareness and vaccine hesitancy) of the intervention effects on HPV vaccination.Assess the sustainability of the intervention in vaccine uptake post-intervention and assess scalability of the program for wider implementation via a future national randomized control trial.

**Table 2 Tab2:** Overview of selected intervention strategies guided by the 4 Pillars™ Program

Pillar Strategy	Level	Intervention Component
Pillar 1: Convenience	Provider-	• Incorporate recommendation of the HPV vaccine with each clinic visit. • Perform HPV vaccination on-site
Pillar 2: Communication and education	Patient-	• Provide patient education on risk of HPV-related cancer and benefit of HPV vaccination
Pillar 3: Enhanced systems	Clinic-	• Provider and staff education on HPV vaccination via an in-service training • Document vaccination in EMR system
Pillar 4: Motivation	Clinic- Provider- Patient-	• Clinic designated Immunization Champion to provide coaching and motivation of regularly tracked vaccination progress • Provide patient check-in, reminders, and motivation for HPV vaccine completion • Communicate vaccination reminders by text, phone, and social media messaging

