#### Data analyses of primary outcomes

For analysis of the primary (HPV vaccination initiation) and secondary endpoints (HPV vaccination completion), the uptake rate of HPV vaccination pre- and post-intervention will be estimated separately with a 95% exact confidence interval using all eligible cases from both phases. The one-sample binomial exact test will be used to test whether the rate after the intervention is higher than the baseline rate (P0 = 13.5%). We will also perform the Chi-square test to compare the rate change between control and interventional phases, which will be exploratory. Logistic regression will be used to further adjust background difference in study population in pre- and post- intervention phases. For the longitudinal data collected from the intervention phase, the data structure holds multi-level information from patients, providers, and clinic levels. The goal of the analyses is to identify the factors that might impact HPV uptake from each level of information, which might lead to the future improvement of implementation strategy. Data will be described using summary statistics (e.g., quartiles, median, mean, standard deviation) for continuous variables and marginal distribution (frequency and percentage) for categorical variables. The univariate association with the HPV vaccination (yes vs. no) will be tested in logistic regression for each variable separately. The change of survey response between baseline and a follow-up time point will be tested by paired tests (e.g., paired t-test, McNemar test). Along with data visualization, all above mentioned descriptive and univariate association analyses will be repeated within each of the three clinics. Data will be pooled to build the multilevel analysis models, we mainly consider using the mixed-effect model and/or Bayesian multilevel modeling, in which the random effect will be considered at provider and clinical levels. We will follow the key modeling considerations listed by J.J. Hox [29] to identify the significant mediators and moderators at different levels that impact the uptake of HPV vaccination.

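### The exact test at n = 317 has 77.0% power, not the stated 80%, and the rejection count of 54 belongs to about 317 patients, not to the 365 or more that the plan expects to analyse

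*Protocol article*

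**What the plan says.** All of this is in the protocol article.

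- **Design claim** (Statistical power): "a sample size of 317 achieves 80% power to detect a superiority difference of 5% (PB-P0) using an exact one-sided test". The level is fixed in the same sentence: "using an exact one-sided test with a significance level (alpha) of 0.05". The section later repeats that the software calculation was for the exact test of one proportion.
- **Rates:** the null is the baseline rate of 13.5%. The target is described as "reasonable to achieve with an uptake rate of 18.5% (PB) after the intervention".
- **Rejection count** (Statistical power): the null can be rejected "after 54 patients have initiated the HPV test". No denominator is attached.
- **Enrolment** (Statistical power): "After taking about 15% of the drop-off rate into account, we plan to include 365 participants among 3 clinics for the intervention phase". The section ends by saying that the number behind the vaccination rate will exceed 365, because status is captured in the medical record without consent.
- **Primary analysis** (Data analyses of primary outcomes): a one-sample exact binomial test of whether the post-intervention rate is "higher than the baseline rate (P0 = 13.5"%), using all eligible cases.
- **Aim 2** (Background, specific aims): "we estimate an uptake rate of" 13.5% or more. The power section gives the formal hypotheses as P at most 13.5% against P above 13.5%.

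**The concern.** The power section names the exact test as the basis of both the sample size and the analysis, so 317, 54 and 80% should all come from one exact binomial calculation. They do not: at 317 patients a cut-off of 54 fixes the power, and it is not 80%. The primary endpoint's published type II error is therefore too low by about three points.

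The second issue is the count. A rejection count is valid only for the denominator it was derived from. The plan prints 54 as the number that allows a claim of success, and the same section says that the analysed number will be larger than 365. Someone who later applied 54 to the enrolled cohort would be claiming success at 54/365 = 14.8%, against a null of 13.5%.

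**Working it through.** **Inputs.** P0 = 0.135, PB = 0.185, one-sided alpha 0.05, n = 317, stated power 80%, stated count 54, allowance about 15%, enrolment 365. All are in the power section.

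**1. Where 317 comes from.** The one-sample normal approximation is

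n = [(z₀.₉₅ √(P0(1−P0)) + z₀.₈₀ √(PB(1−PB))) / (PB−P0)]²

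= [(1.645 × √(0.135 × 0.865) + 0.842 × √(0.185 × 0.815)) / 0.05]² = 316.05, rounded up to 317.

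The stated n is reproduced by this approximation. Other approximations give different sizes: 289 with the null variance only, 373 with the alternative variance only, 336 or 355 with a continuity correction, and 331 with the arcsine transformation.

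**2. Exact test at n = 317.** The critical count is the smallest r with P(X ≥ r | 317, 0.135) ≤ 0.05. Power is P(X ≥ r | 317, 0.185).

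| Cut-off r | Type I error | Power |
|---|---|---|
| 53 | 5.85% | 81.2% |
| 54 | 4.25% | 77.0% |

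So 54 is the correct count. It gives 77.0% power, 3.0 points below the stated figure. A power above 80% at this n needs a cut-off of 53, which breaks the 0.05 level.

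**3. The n at which exact power is 80%.** Exact power moves in a saw-tooth as n grows. It first reaches 80% at n = 333 (count 56, alpha 4.86%, power 80.5%). It last falls below 80% at n = 355 (79.95%) and stays at or above 80% from n = 356.

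**4. The count at other denominators.** The exact critical count is 54 for n = 314 to 320 and for no other n.

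| n analysed | Exact count | Actual alpha | Exact power | Type I error if 54 were used |
|---|---|---|---|---|
| 317 | 54 | 4.25% | 77.0% | 4.25% |
| 321 | 55 | 3.7% | 75.6% | 5.2% |
| 365 | 61 | 4.6% | 82.8% | 25.5% |
| 373 | 62 | 4.9% | 84.2% | 31.2% |
| 400 | 66 | 4.9% | 86.4% | 52.2% |

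For every n from 365 to 2300, exact power with the correct count is at least 80.4% (the lowest value is at n = 367). The upper end of 2300 is an assumption for the range. It is the approximate number of eligible records that the plan gives for the control phase, not a stated size for the intervention phase.

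**5. The allowance.** 317 × 1.15 = 364.55, rounded up to 365, which reproduces the plan's figure. Allowing for a 15% loss means dividing: 317/0.85 = 372.9, or 373. Going from 365 to 317 is a loss of 48/365 = 13.2%. A full 15% loss from 365 would leave about 310 (count 53, alpha 4.2%, power 75.9%).

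**The case against.** The strongest reply is that the plan's error rates are sound in practice. The primary analysis is an exact binomial test, which takes its p-value from the n actually analysed and so holds alpha at 0.05 whatever that n is. The sentence with 54 stands in the power section, shortly after 317 is introduced, and is naturally read as the critical value for that n. Nothing says that 54 will be applied to 365. Power is also protected: the plan expects to analyse more than 365, where exact power is at least 80.4%, and survey drop-off does not remove an outcome that is read from medical records and the immunisation registry.

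Most of this stands. A reader might infer that the primary test has a 25.5% type I error, that 54 was miscalculated, or that the trial is underpowered. The documents support none of these. The 25.5% arises only if 54 is carried over to 365, 54 is correct for 314 to 320, and power at the expected size is adequate. The 75.9% at 310 likewise applies only if drop-off removes primary-outcome data, which the plan's data source makes unlikely.

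The reply does not rescue the sentence that attaches 80% exact power to 317. Nor does it remove the mismatch between a success count without a denominator and an analysis set that the same section says will be larger than 365.

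**Conclusion.** The power statement is wrong as written: 77.0%, not 80%, for the named test at n = 317. This follows from the plan's own inputs, with 13.5% taken as a fixed null rate. The count of 54 is correct at 317 but does not fit the sample that the plan describes. The count at 365 is 61 and rises with n.

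This is an error of statement, not a failure of the design. If at least 365 patients are analysed, 80% power is met, and the exact test at the actual n controls alpha.

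Two smaller points are matters of wording. The allowance was multiplied rather than divided, a gap of 8 patients (about 2%) against a loss described only as about 15%. Aim 2 includes the null value, but the formal hypotheses in the power section are correct, so the analysis is unaffected.

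**What to change.** In the power section:

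1. Either restate exact power as 77.0% at n = 317 (count 54, actual alpha 4.25%), or quote it at the n to be analysed. At 365 that is count 61, actual alpha 4.6%, power 82.8%.
2. Say that 54 is the count for n = 317, and that rejection is decided by the one-sided exact binomial test at the n actually analysed. Do not simply replace 54 with 61 as a fixed rule, and do not limit the analysis to 365 for this purpose. The plan describes a larger set based on medical records, and 61 would be just as tied to one denominator.
3. Describe the step from 317 to 365 as an allowance of about 13%. If 15% is meant, the figure is 373.

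In Aim 2, write the hypothesis as a rate above 13.5%, to match the stated alternative.

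The cost is a few sentences of rewording. Items 1 and 2 need no added patients and no change to the test or the data collection.
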